## 1.5 OBJECTIVES AND RATIONALE FOR PROPOSED TRIAL

### 1.5.1 OBJECTIVES

The objectives of this Phase IIb clinical trial are:

- 1) To determine the vaccine efficacy of each combination HIV vaccine regimen compared to placebo, in preventing acquisition of HIV infection
- 2) To determine the effectiveness of TAF/FTC PrEP as a function of the effectiveness of TDF/FTC PrEP and hypothetical placebo
- 3) To determine the safety of (i) each combination HIV vaccine regimen compared to placebo and (ii) TAF/FTC PrEP in comparison to TDF/FTC PrEP
- 4) To understand the trial results in the context of risk and adherence behaviours, knowledge attitudes and perceptions of participants, study staff and the wider community

## 1.5.2 RATIONALE

PrEPVacc is a phase IIb, three arm, two stage HIV-1 prophylactic vaccine trial with a concurrent randomisation to compare TAF/FTC to TDF/FTC as PrEP. The design is efficient as two different combination vaccine regimens will be evaluated, as well as an experimental PrEP agent, and pragmatic in that it mirrors the logical way that PrEP would be used if these regimens were to proceed into a public health programme, supporting the vaccine schedule through to optimal immunogenicity 2 weeks after the third immunisation.

The trial is designed to detect vaccine efficacy of **public health relevance**. In light of the high level of effectiveness demonstrated in the PrEP trials (up to 86% reduction in HIV incidence) and in programmes (near perfect protection), the investigators consider that an HIV vaccine regimen would have to observe a reduction in HIV incidence of around 70% to justify implementation. Although this is higher than seen previously, the reduction in HIV in RV144 during the first 12 months of follow-up was 60% suggesting higher vaccine efficacy is possible. With a target vaccine efficacy of 70% reduction HIV, an observed reduction of 47% would be statistically significant in the final trial analysis.

The assumptions underlying the sample size calculation for the vaccine trial include an HIV incidence of 4/100 person years. Although there is evidence from previous studies and surveillance data to support this high incidence across the totality of the participating centres, there is considerable uncertainty. Incidence is generally declining in the region as testing expands, treatment is started promptly and access to PrEP increases. In order to determine the sample size for each centre, to refine the recruitment strategy and facilitate timely enrolment in the trial, enrolment in a Registration Cohort began in June 2018 under separate protocols in each centre.

### ***Rationale for the proposed vaccination schedule***

The vaccination schedule in the original RV144 trial included ALVAC®HIV vaccine vCP1521 administration at time 0 and Month 1 and ALVAC® HIV vaccine vCP1521+ AIDSVAX® B/E at Months 3 and 6. The vaccine efficacy (VE) observed in the first year approached 60%, and waned over the 3.5 years of follow-up to an overall VE of 31%.

Building on the RV144 schedule and results, we have altered the PrEPVacc vaccination schedule with the aim of improving the magnitude and durability of vaccine-elicited immune responses beyond those observed in RV144. These changes have been made under the scientific assumption that improvements of immune responses will translate into improvements in vaccine efficacy. These alterations include:

- 1) Introduction of a protein vaccine from the beginning as antibody responses were not detected for the first 12 weeks in the RV144 trial which did not include the combination of ALVAC/AIDSVAX® B/E until week 12. Several phase I trials have clearly shown that co-administration is well-tolerated and results in earlier induction and higher magnitude and durability of protective V1V2 antibody responses over 18 months. The EV06 trial evaluated co-administration of DNA-HIV-PT123 with AIDSVAX® B/E protein at week 0, 4 and 24, as proposed in PrEPVacc, and showed the induction of potent binding and neutralizing antibody responses. A more recent analysis of the EV06 IgG binding antibody responses against a multi-clade panel of V1V2 constructs performed by [name] group from Duke University, revealed potent cross clade responses ([name], personal communication).
- 2) Addition of the boost at week 48 is expected to prolong the durability of the peak immunogenicity compared to RV144.

### ***Rationale for the evaluation of TAF/FTC as PrEP***

TDF/FTC is very safe, but renal and bone toxicity are concerns with long term use, especially as individuals age and acquire co-morbidities that could aggravate these toxicities. TAF/FTC requires a

smaller concentration of tenofovir than TDF/FTC with two advantages: reduced toxicity and reduced manufacturing costs. In light of the reduced costs, it is likely that TAF/FTC will replace TDF/FTC in settings where generic drugs are used. The DISCOVER trial compared TAF/FTC to TDF/FTC in MSM and transgender women in North and South America and Europe observing only 7 infections in the 2,694 TAF/FTC participants compared to 15 in the 2,693 TDF/FTC participants. Although regulatory authorities may feel able to extrapolate the results to heterosexual men, this is unlikely to be the case for women due to the differences in tissue penetration. The lack of clinical effectiveness data for TAF/FTC when used as PrEP in heterosexual populations, particularly women, could be a critical gap if TAF/FTC replaced TDF/FTC as the main drug in Sub-Saharan Africa and other settings where the dominant transmission route is heterosexual sex.

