#### 1.4.6 TAF/FTC As PrEP

Emtricitabine (FTC) and Tenofovir alafenamide (TAF) is approved for use as treatment in several jurisdictions, including in at least two of the participating countries. It is also approved for PrEP by FDA except in persons who have receptive vaginal sex. TAF is a pro-drug of tenofovir with rapid and sustained cellular loading, but lower genital tract tissue concentrations compared to TDF/FTC.

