## 6.2 PROCEDURES DURING THE SCREENING PERIOD

### 6.2.1 INFORMED CONSENT

At the screening visit, participants will have the opportunity to ask questions and have a full discussion of the information provided in writing and/or visually and verbally. This will include the following key messages:

- ▶ That there is a 1 in 3 chance that they are assigned to a placebo injection, but this may change during the trial to 1 in 2 if one of the trial arms is discontinued or interrupted
- ▶ That we do not know if the active vaccine combination regimens will prevent HIV
- ▶ That condoms and PrEP are known to reduce the risk of acquiring HIV when used or taken consistently
- ▶ That pregnancy is to be avoided until 18 weeks after last vaccine as the safety of vaccines is not known
- ▶ That the immune responses made by their bodies to the vaccines could show up in future HIV tests

Participants will be shown images of the PrEP pills. They will be asked if they discussed their participation with anyone and if any problems arose because of this. If they wish to proceed, they will be given an informed consent form to read and sign prior to any investigations. It will be dated and countersigned by the investigator or delegated person, who explained the study to them. If they are unable to read and write, they will be asked to place their thumbprint on the informed consent in the presence of an independent witness who has been present for the discussion. The witness cannot be a member of the site study staff.

A copy of the consent form will be provided to the participant and one copy kept in the study file according to local procedures. If they have not already done so, they will be encouraged to discuss their participation with their partners, friends and family.

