### 6.3.1 ELIGIBILITY

Study staff will check that participants understand the key messages contained in the information sheet and listed in [section 6.2.1](#).

Study staff will review the routine laboratory parameters and screen for STIs collected at screening and determine whether there are any clinically relevant abnormalities that require further investigation prior to randomisation. STIs will be treated appropriately, but the participant can proceed to randomisation on the day, if otherwise eligible.

Participants will review any new adverse events or new medications since the screening visit and for female participants, any changes in contraception. All this information will be recorded on the appropriate CRF according to the SOM. The Risk assessment CRF will also be administered.

Study staff will review the risk of the participant acquiring HIV again to see if anything has changed since screening, and conduct a point of care HIV test in accordance with the LAP.

For female participants of childbearing potential a pregnancy test will be performed by analysis of a urine sample for Human Chorionic Gonadotrophin (HCG) and a negative result will be confirmed before each injection.

The review of Eligibility will be completed using the appropriate CRF.

Prior to randomisation, blood will be collected for 4th generation ELISAs, and to store for future immunological assays, HIV RNA, and intracellular tenofovir diphosphate levels.

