## 9.4 INTERIM MONITORING & ANALYSES

An IDMC Charter will be drawn up that describes the membership of the IDMC, relationships with other committees, terms of reference, decision-making processes, and the timing and frequency of interim analyses (with a description of stopping rules and/or guidelines, if any).

The IDMC will regularly review safety data and incident HIV data by randomised arm as described in the charter (for both randomisations).

In addition for the vaccine trial, there is one formal planned interim analyses to be performed when approximately 7 HIV incident cases are observed in the control arm. Recommendation for possible discontinuation of further enrolments and vaccines for those already enrolled to intervention arm(s) will be made from the results of this analysis.

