## 11.2 ETHICAL CONDUCT

### 11.2.1 ETHICAL CONSIDERATIONS

PrEPVacc is assessing interventions to reduce the risk of HIV acquisition and therefore sites will be recruiting individuals at risk of acquiring HIV. Populations at risk of HIV are frequently vulnerable because of the intersecting social syndemics of poverty, violence, drug and alcohol addiction, and depression. In PrEPVacc participants will be provided with condoms and PrEP, both of which are known to prevent HIV, but the study supply of PrEP will cease once they have completed three injections plus two weeks follow-up. Study staff will inform participants where they can access PrEP locally and support them to do so where this is possible, and continue to supply condoms. Please see section 1.5 for context and rationale.

The vaccines are not licensed and some have only been administered to a few hundred individuals so there may be adverse events that we have not anticipated.

Participants who receive active vaccine may develop antibodies that lead to a positive point of care HIV test in future, including after the trial has finished. Study staff will provide participants with an identity card verifying their participation in a HIV vaccine trial and continued access to laboratory testing and certification of status.

The materials to support informed consent will be developed to ensure that participants understand the risks and benefits of participation, in particular that the design includes a placebo vaccine, that no-one knows whether the active vaccines can reduce the risk of HIV, that they may require additional tests after the study to distinguish between a vaccine reaction and HIV infection, and that study will only supply PrEP for 26 weeks. The materials developed will take account of the level of literacy in each centre. Participants who are not able to read will be asked to provide their thumbprint. They will be accompanied by a witness of their choice who can read and who will be asked to sign the consent form.

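### The key consent message and ethics text call PrEP proven without separating TAF/FTC from TDF/FTC, although the protocol says TAF/FTC lacks clinical effectiveness data in women

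*Protocol*

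**What the plan says.** On the evidence, section 1.4.6 says of TAF/FTC: "It is also approved for PrEP by FDA except in persons who have receptive vaginal sex". It also notes lower genital tract tissue concentrations than with TDF/FTC. Section 1.5.2 (rationale for evaluating TAF/FTC) accepts that regulators might extend the existing trial result to heterosexual men, but says "this is unlikely to be the case for women due to the differences in tissue penetration". It concludes: "The lack of clinical effectiveness data for TAF/FTC when used as PrEP in heterosexual populations, particularly women, could be a critical gap".

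On what participants are to be told, the key messages in section 6.2.1 include "That condoms and PrEP are known to reduce the risk of acquiring HIV when used or taken consistently". The same list says of the vaccines: "That we do not know if the active vaccine combination regimens will prevent HIV". Section 6.3.1 then requires a check before randomisation: "Study staff will check that participants understand the key messages contained in the information sheet", with a pointer back to the list in 6.2.1. Section 11.2.1 says "participants will be provided with condoms and PrEP, both of which are known to prevent HIV". Its list of what consent materials must convey covers the placebo, the unknown efficacy of the vaccines, the possible need for extra HIV tests and the limited duration of PrEP supply. It does not mention that the effectiveness of TAF/FTC in women is unknown.

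Section 9.1 randomises PrEP 1:1, stratified by centre and gender, with TAF/FTC as the experimental arm and no restriction by sex.

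**The concern.** The protocol treats the effectiveness of TAF/FTC in women as an open question where it justifies the trial, and as settled where it sets out what participants should understand. For the vaccine randomisation the uncertainty is disclosed as a key message. For the PrEP randomisation the corresponding message expresses certainty, and the only condition attached is consistent use.

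Informed choice is at stake. A woman deciding whether to enter a 1:1 randomisation between the two drugs needs to know that one of them has not been shown clinically to protect during receptive vaginal sex. That is the main uncertainty of the PrEP comparison, and the listed messages do not mention it.

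**Working it through.** The point is textual, so the check sets the sections side by side and verifies the one related figure.

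**1. Evidence cited for TAF/FTC as PrEP.** The only clinical effectiveness result is the phase III trial in MSM and transgender women reported in section 1.4.6: 7 infections in 4370 person-years on TAF/FTC and 15 in 4386 on TDF/FTC.

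- Rate ratio = (7/4370)/(15/4386) = 0.468.
- Standard error of the log ratio = √(1/7 + 1/15) = 0.458.
- 95% CI = 0.468 × exp(±1.96 × 0.458) = 0.191 to 1.149.

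This reproduces the stated 0.47 (0.19 to 1.15). The figure is correct, but it comes from a population that does not fill the gap named in 1.5.2. Otherwise section 1.4.6 cites a monkey challenge study, a single-dose pharmacokinetic study in 24 women, and a 14-day study in 72 women with drug levels and an ex-vivo infection model. None of these is a clinical effectiveness result. The accurate summary is therefore no clinical effectiveness data in heterosexual populations, particularly women. It is not true that there are no data in women at all.

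**2. Evidence against message.**

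| Topic | Evidence sections | Consent and ethics text |
|---|---|---|
| Vaccines | Efficacy unknown | Stated as unknown (6.2.1, 11.2.1) |
| TDF/FTC | Effectiveness trials and WHO recommendation (1.3, 1.5.2) | Stated as established |
| TAF/FTC, receptive vaginal sex | Outside FDA approval; no clinical effectiveness data (1.4.6, 1.5.2) | Stated as established, through the undivided term PrEP |

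The first two rows agree. The third does not.

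**3. Does PrEP here mean only the established drug?** In 6.2.1 the word could be read as the class in general. In 11.2.1 it cannot, because that sentence is about the PrEP provided in this trial. With 1:1 allocation and the minimum target, 1668/2 = 834 participants receive TAF/FTC.

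**4. Does the protocol separate the drugs elsewhere?** Yes. Sections 5.5.6 and 7.2.1 distinguish them for pregnancy and say that TAF/FTC data are insufficient. The undivided wording in 6.2.1 and 11.2.1 is therefore not a convention used throughout.

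**5. Who receives the message?** It is given at screening and checked at enrolment, before allocation is known. It reaches every woman who considers joining, and not only those later allocated TAF/FTC.

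**The case against.** The strongest reply is that what participants are told stands in the information sheet and consent form, which are separate documents and not shown. The lists in 6.2.1 and 11.2.1 are not presented as exhaustive, and under 11.2.2 each national ethics committee determines the content of its country's materials. A TAF/FTC caveat may well be there. This stands. A reader might infer that women allocated TAF/FTC are in fact told that unproven protection is proven; the documents at hand cannot show that.

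The reply does not remove the inconsistency. Staff must check the messages listed in 6.2.1, and 11.2.2 submits the protocol and its key messages to the sponsor's ethics committee for approval. A caveat placed only in the information sheet would sit beside a listed message that does not carry it.

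Two stronger readings also fail:

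- **Extra infections.** A reader might attach an infection count to the wording. Any such count needs an assumed shortfall of TAF/FTC in women, which the protocol does not give. It would also follow from the randomisation and not from the consent text, so correcting the message would not by itself avert those infections.
- **Monitoring pooled over gender.** Section 9.4 says "The IDMC will regularly review safety data and incident HIV data by randomised arm", which might suggest that a problem in women would be averaged with men. The sentence goes on to refer to the charter, which is not shown, and section 9.5.2 already foresees an analysis by gender if endpoints suffice. Pooling is not documented.

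It is likewise not shown that women would rely on TAF/FTC in place of condoms. Counselling promotes both, and condoms continue to be supplied.

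**Conclusion.** The inconsistency is real and lies in the protocol's own text. Sections 1.4.6 and 1.5.2 treat TAF/FTC in women as clinically unproven, while sections 6.2.1 and 11.2.1 call PrEP proven with no distinction by drug or sex. Section 11.2.1 is the clearer case because it refers to the PrEP supplied. Section 6.2.1 matters more in practice because its messages are the ones checked before randomisation.

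The statement is unsupported for women who receive TAF/FTC. Their number is some part of about 834 at the minimum target and cannot be given more closely, since the share of women is not stated. No sample size, power or error rate changes. The conclusion rests on the protocol text alone and would be softened, though not removed, by a caveat in the information sheet.

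**What to change.** Reconcile sections 6.2.1 and 11.2.1 with 1.4.6 and 1.5.2:

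- In both sections, limit the statement about established protection to condoms and TDF/FTC.
- Add to the key messages in 6.2.1, so that it is checked at enrolment under 6.3.1, that it is not yet known how well TAF/FTC protects during receptive vaginal sex.
- Add the same point to the list in 11.2.1 of what consent materials must convey, and confirm that the information sheet agrees.

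The cost is a few sentences and the matching ethics submission. No drug, dose, allocation or clinical rule changes. The small downside is that, PrEP being open-label, women on TAF/FTC may change their condom or PrEP use. The behaviour and adherence data in sections 5.9.2 and 6.9.1 already record this.

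Optionally, the IDMC charter could show HIV infections by PrEP arm separately for women and men, if it does not already. That is a suggestion and not part of the finding.

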### ***Ethical considerations in the provision of PrEP in prevention trials***

TDF/FTC PrEP has been strongly recommended by the World Health Organisation as a risk reduction strategy to be provided to populations with substantial risk of acquiring HIV since 2015. Countries continue to explore how to integrate PrEP through demonstration projects and national programmes, including , South Africa, Tanzania and Uganda, and have included PrEP in their national policies. Kenya is one of the most advanced countries in the world with respect to implementation of PrEP, with between 33-44% of eligible individuals from key populations (men who have sex with men and female sex workers respectively) initiating PrEP in a national programme. However, much smaller proportions return for more PrEP at three months and it is not yet entirely clear why although concerns about side-effects and stigma, and low perceived need of additional risk reduction strategies, which are potentially life-long, all contribute. The greatest efforts to generate market demand are in the US, where PrEP is widely advertised on social media and even television. Nonetheless penetration is less than 10% of those estimated to be in need according to the US Centre for Disease Control, and again retention in PrEP programmes is low with a median of 8 months in a recently reported study in San Francisco. This is explained in part by the co-payments required by PrEP users, even when the drug itself is free. In England, PrEP has been available free of charge since March 2020.

Guidelines are now clear regarding the provision of TDF/FTC or TDF/3TC (collectively referred to as TD/XTC) PrEP in prevention trials, with two recommended approaches to ensure provision of PrEP:

- 1) TD/XTCX can be the control arm
- 2) TD/XTCX is provided to all participants for the duration of the trial in the study clinic or through referral to locally available sources

We have chosen to evaluate vaccines and PrEP in a way that a national HIV vaccine programme would be likely to combine the two with daily study PrEP to support the time to peak immune responses and thereafter available to all who wish to continue. We recognise the potential for a conflict of interest for staff when promoting PrEP in a vaccine trial and hope including PrEP as a study drug will address this, and that uptake and adherence will be higher as a consequence, potentially overcoming misgivings that participants may have had about taking PrEP when they enrolled. The data gathered in the preceding Registration Cohort has assisted in mobilising PrEP services, and therefore it is anticipated that investigators will be able to support participants motivated to continue PrEP after they complete the first three immunisations through access in the community or direct provision to a sustainable supply. The Registration Cohort has confirmed that new HIV infections occur even when PrEP is available, particularly in female participants, underscoring the need for other interventions to prevent HIV.

## 2 SELECTION OF SITES/CLINICIANS

The trial Sponsor has overall responsibility for site and investigator selection, advised by the Trial Steering Committee.

### 2.1 SITE/INVESTIGATOR INCLUSION CRITERIA

To participate in the PrEPVacc trial, investigators and clinical trial sites must fulfil a set of basic criteria that have been agreed by the PrEPVacc Trial Management Group (TMG) and are defined below. Only sites that have participated in the Registration Cohort and built sufficient capacity can participate in the PrEPVacc trial.

